##### Quality of life

2.3.2.4

QoL will be evaluated by Multiple Sclerosis Quality of Life-29 (MSQOL-29) (38), a multidimensional health-related QoL measure that combines both generic and MS-specific items into a single instrument. The questionnaire consists of 29 items, divided into 7 subscales related to physical functioning, pain, emotional well-being, energy, cognitive function, health stress, sexual function, change in health, social function, health perception and overall QoL (38).

##### Occupational factors

2.3.2.5

The potential exposure to harmful agents in the workplace will be assessed through a specific questionnaire aimed at identifying the exposure to the entire working life of the subjects involved. The information collected regarding the duration of each work activity and the tasks performed throughout work life will be investigated. This will include the specific sector(s) of employment, the main tasks performed, and the workplace location(s). Following this information, the related International Standard Classification of Occupation (ISCO) code will be assigned (40). The ISCO code will be adopted to determine the level of occupational risk for SM of the involved subjects, according to four classes: (1) work activities associated with specific occupational risks connected with SM (such as agricultural workers, offshore workers, and hairdressers (41); (2) work activities associated with occupational risks less likely connected with the SM diagnosis (such as exposure to toxic oil well fumes, low-frequency magnetic fields, and pesticides (41); (3) work activities not directly connected with increased risk for SM, but identified as potential causes of relevant professional diseases through inflammatory pathways (e.g., exposure to carcinogenic and mutagenic agents, toxicants, ionizing radiation, etc.); (4) work activities not associated with specific relevant occupational diseases (e.g., office workers, trade workers, unemployed). In the case of multiple activities during working life, the prevalent exposure, namely the one correlated with the longest working period of the subject, will be considered.

#### Internal exposome variables (including the endpoints of the study)

2.3.3

Blood samples will be analysed to evaluate miRNA expression, neurofilament proteins, levels of pro- and anti-inflammatory cytokines, and vitamin D levels. Samples will be collected by trained research nurses without requiring participants to fast. Each sample will be anonymised using a progressive code, accompanied by the participant’s sex and date of birth. The anonymised samples will then be treated for pre-analytical processing, including centrifugation, separation, and storage.

During the pre-analytical phase, the absence of hemolysis is required for sample suitability; any hemolysis detected must be documented. Additionally, samples must be maintained at room temperature until the separation process is complete.

For the analysis of miRNA expression and vitamin D levels, and other biochemical parameters, blood specimens will be collected in tubes designed for specific serum samples (four 3.5 mL tubes without additives) and plasma samples (three 3.5 mL tubes containing either EDTA or citrate to prevent coagulation).

Plasma samples will be obtained by centrifugation of the EDTA- or citrate-containing tubes. Both serum and plasma samples will be centrifuged at 3,000 rpm for 15 min and processed within 2 h of collection. The processed samples will then be divided into aliquots (eight for serum and six for plasma), each with a minimum volume of 500 μL, and stored at −80°C until analysis.

The miRNA expression, as well as the neurofilament protein (NfL), cytokine, and levels of 25(OH)D vitamin measurements, will be assessed.

Stool samples will be collected to analyze the intestinal microbiota and will be collected by the PwMS after they are accurately instructed by a member of the research team on how to collect, store, and transport samples, according to the following inclusion criteria: (i) absence of fever and gastroenteritis; (ii) absence of diarrhea for more than 24 h in the previous 7 days; (iii) no antibiotic treatment in the previous 7 days. Similarly, the nasal swab samples will be collected using flexible flocked swabs and conserved in specific tubes containing transport medium, making them compatible with downstream sequencing assays.

Stool and nasal samples will then be anonymised by the trained dietitians and biologists who received them, using a progressive code and stored at −80 °C, until the analysis.

##### MicroRNAs expression levels (primary endpoints)

2.3.3.1

The differential expression of a set of 5 specific circulating plasma miRNAs from the blood of each pwMS will be measured. The set of miRNAs has already been selected based on their significantly deregulated expression in MS, as evidenced in a bioinformatic analysis conducted using several public microarray databases from Gene Expression Omnibus (GSE61741, GSE31568, GSE17846, GSE21079, GSE74579, GSE215450).

We focused on those miRNAs showing the most coherence in terms of regulation direction (i.e., statistically significant up or down-regulation) across the databases. The analysis allowed us to obtain a list of miRNAs that were consistently up- or down-regulated in the comparison between MS and healthy samples. In particular, plasma samples of our cohort were analysed to quantify the level of expression of miR-30a-5p, miR-146a-5p, miR-664, miR-330, and miR-574-3p normalised on U6 expression. Notably, three miRNAs (miR-30a-5p, miR-146a-5p, miR-664) were up-regulated in four databases, and two miRNAs (miR-330, miR-574-3p) were down-regulated in three databases. Interestingly, miR-146a (42), miR-30a (43), miR-330 (44), and miR-574 [0.1002/ana.23880] have already been associated with MS.

Moreover, they have a key role in characterising inflammation and oxidative stress. In particular, miR146a acts as a negative regulator of the NFκB pathway, modulating pro-inflammatory cytokines, and has been shown to influence reactive oxygen species (ROS) production in various pathological conditions (45). miR30a also plays a crucial role in regulating inflammatory factors and oxidative stress factor expression by targeting Neurod 1 and the MAPK/ERK pathway (46). The binding of miR-574-5p to TLR8/7 triggers the TLR signalling pathway, leading to the induction of interferons, inflammatory cytokines and autoimmune signalling. These findings suggest that miR-574-5p is not only an important epigenetic regulator of gene expression, but also an important regulator of immune and inflammatory responses (47). Finally, miR330 is associated with the inflammatory responses and oxidative stress mediated by miR-330-5p/EPHB3 axis in neuroinflammation and cognitive dysfunction (48).

A portion of serum samples will be collected and immediately frozen at −20 °C. After being transported, serum samples will be thawed, and the circulating RNAs will be extracted (Trizol, Thermo Fisher Scientific). After a step of miRNA-specific reverse transcription (TaqMan miRNA reverse transcription kit, Thermo Fisher Scientific; Mir-X miRNA First-Strand Synthesis Kit, Takara), the copy-DNA obtained will be used as the template for Real Time-qPCR analyses of selected miRNAs by Singleplex TaqMan miRNA assay reactions and/or in SybrGreen-based RTqPCR (SIC).

The method of Livak et al. (49) will be applied for the comparative analysis of the relative expression of the selected miRNAs in serum samples, considering different combinations of the external exposome variables.

Specifically, RT-PCR returns the number of cycles that the samples underwent before they were detected, reported as a value known as the Cycle Threshold (CT). The CT values vary logarithmically with expression levels. ΔCT values are calculated by subtracting the CT value of the endogenous control for a given sample (or the mean of the CT values of the endogenous controls if more than one exists) from the CT value of the gene for the given sample. The ΔΔCT is calculated by subtracting the ΔCT of an experimental sample from a control sample. Fold change is calculated by raising 2 to the power of the negative ΔΔCT value since CT values are related to the amount of miRNA or gene logarithmically. A statistical analysis will be applied to highlight the differences in the expression of each miRNA in the two populations.

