#### Sample size calculation

2.4.1

Regarding the background for the sample size calculation, to identify a small number of miRNAs to be validated as diagnostic MS-associated miRNA profiles in RT-qPCR on serum samples, a bioinformatic analysis was preliminarily conducted and described in section 2.2.3 Internal exposome variables.

As for the sample size calculation, to validate variation among the selected MS diagnostic miRNA, in response to urban air pollution, urbanisation, lifestyle and QoL components of the external exposome, the differential expression (ΔCT) for each miRNA will be considered as the endpoint measure. To compare the mean difference of ΔCT for each miRNA among exposure groups and to include the possible modulating effect in terms of accommodating covariates, negative binomial generalised linear models (GLM) will be used. Sample size has been calculated accordingly (58) through an estimating procedure based on a representative exemplary dataset created for a single miRNA comparison among two groups of pwMS defined by a specific external exposure variable and including a vector of covariate variables for the miRNA sample. The alternative hypothesis that the logarithm of miRNA fold change is different from zero against the null hypothesis of a log fold change equal to zero, by the likelihood ratio test statistic, will also be tested.

The minimum number of pwMS necessary to achieve 80% of power, considering a desired minimum miRNA fold change between 1.1 and 4.5, was 168. Therefore, 200 eligible pwMS who meet the inclusion criteria and sign the informed consent will be included in the study, considering a 15% dropout at the blood sampling stage.

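### All five primary ΔCT endpoints share one named reference, U6, and the article states no step that would show whether U6 itself varies with exposure

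*Protocol article*

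**What the plan says.** Section 2.3.3.1 (MicroRNAs expression levels) defines the primary endpoint as "The differential expression of a set of 5 specific circulating plasma miRNAs" and names the reference: "miR-664, miR-330, and miR-574-3p normalised on U6 expression". The same section gives the arithmetic: "ΔCT values are calculated by subtracting the CT value of the endogenous control for a given sample". It then adds a general allowance, "or the mean of the CT values of the endogenous controls if more than one exists", without naming a second control. Fold change follows from "Fold change is calculated by raising 2 to the power of the negative ΔΔCT value".

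Section 2.4.1 (Sample size calculation) confirms the analysis scale: "the differential expression (ΔCT) for each miRNA will be considered as the endpoint measure".

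The nearest safeguard is pre-analytical. Section 2.3.3 says that "the absence of hemolysis is required for sample suitability; any hemolysis detected must be documented". In section 2.4.5, item (e) adjusts the miRNA models for confounders and validated biomarkers, and item (g) reports Benjamini–Hochberg q-values.

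No section describes a second reference, a comparison of U6 CT across exposures, or a repeat of the primary models under another normaliser.

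**The concern.** With a single shared reference, a shift in that reference cannot be told apart from a panel-wide biological effect. If U6 CT moved with an exposure, five endpoints would move together. A reader would naturally take agreement across five miRNAs as corroboration, when it would be one artefact counted five times.

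The analysis steps described do not separate the two explanations. The q-values deal with chance findings among many tests, not with an error common to all of them. The haemolysis rule concerns whether a sample is usable. Covariate adjustment could absorb part of a shift that travels with cytokines or neurofilament, but it does not show whether a shift exists.

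The normaliser is a choice that the article states, so this is not a detail merely left to another document.

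**Working it through.** **Inputs from the article.** Five miRNAs; reference U6; ΔCT = CT(miRNA) − CT(reference); fold change 2^(−ΔΔCT); target fold change 1.1 to 4.5; 168 evaluable patients for 80% power.

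**Assumptions, because the article does not give them.** Two-sided α of 0.05, an 84 vs 84 exposure split, and CT standard deviations of 0.5 to 1.0 for U6 and for each miRNA.

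**The plan's own figure.** The dropout step is consistent: 168/(1 − 0.15) = 197.6, so 198, against 200 planned. The 168 cannot be reproduced, because neither α nor a dispersion is stated. Under a simple two-means approximation it implies a ΔCT SD of 0.32 at 1.1-fold. The point below does not depend on it; 1.1 serves only as a benchmark.

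**Step 1: bias.** Suppose no miRNA changes and U6 CT is δ higher in the exposed group. Each ΔCT falls by δ. With ΔΔCT taken as exposed minus unexposed, each of the five shows a fold change of 2^δ (reversing the order inverts all five alike). For a continuous exposure in a linear model, the exposure coefficient for ΔCT equals the coefficient for the miRNA CT minus that for the U6 CT, so the same quantity is subtracted from all five.
- 1.1-fold: δ = log2(1.1) = 0.1375 cycle
- 1.41-fold: δ = 0.5 cycle
- 2.0-fold: δ = 1 cycle
- 4.5-fold: δ = log2(4.5) = 2.17 cycles

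**Step 2: how often it would produce false findings.** Simulation: 3000 runs, five miRNAs unrelated to exposure, U6 and miRNA CTs independent, t-tests on ΔCT, Benjamini–Hochberg across the five.

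| U6 SD / miRNA SD | δ | At least one q < 0.05 | All five | All same sign |
|---|---|---|---|---|
| 0.7 / 0.7 | 0 | 4.6% | 0.1% | 33% |
| 0.7 / 0.7 | 0.1375 | 18.8% | 1.6% | 56% |
| 0.7 / 0.7 | 0.5 | 97.1% | 71.7% | 99.8% |
| 1.0 / 1.0 | 0 | 4.7% | 0.2% | 33% |
| 1.0 / 1.0 | 0.1375 | 10.5% | 0.6% | 45% |
| 1.0 / 1.0 | 0.5 | 75.8% | 27.8% | 95% |
| 1.0 / 0.5 | 0 | 4.0% | 0.7% | 60% |
| 1.0 / 0.5 | 0.1375 | 10.9% | 3.2% | 69% |
| 1.0 / 0.5 | 0.5 | 84.4% | 66.0% | 99% |

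At 0.14 cycle a single null test is significant about 10% of the time (CT SDs of 1.0, so a ΔCT SD of 1.41) to 24% (CT SDs of 0.5, so a ΔCT SD of 0.71). The shift must be nearer half a cycle before panel-wide false findings become common. Even at δ = 0, all five estimates share a sign in 33% to 60% of runs, against 2 × 0.5^5 = 6% for independent tests, because the reference is common to them.

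**Step 3: precision.** If U6 and target CT have equal SDs and correlation ρ, the SD of ΔCT relative to that of the target is √(2 − 2ρ): 1.41 at ρ = 0, 1.00 at ρ = 0.5 and 0.77 at ρ = 0.7. If the U6 SD is half the target SD, it is √(1.25 − ρ): 1.12, 0.87 and 0.74. The article gives no ρ.

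**Step 4: what a check of U6 could show.** The 95% half-width for a U6 CT difference is 1.96 × SD × √(2/84) = 0.30 × SD, that is 0.15 cycle at SD 0.5 and 0.30 at SD 1.0. A significance test would detect a 0.1375-cycle difference with power of only 43% and 14% respectively. Across 20 independent null exposures (an illustrative number) the chance of at least one result below 0.05 is 1 − 0.95^20 = 64%.

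**The case against.** The strongest case against has four parts.

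- **The document contains no evidence that U6 is unstable.** A reader might infer that U6 is a known poor reference in cell-free blood and that the primary endpoint is therefore biased. The article does not support this. It gives no data on U6 in plasma or serum, and the premise would have to come from outside sources. This part stands: what remains is a risk without a guard.
- **It is a condensed article.** Reference-stability checks and spike-ins may sit in a laboratory procedure that is not shown, the U6 sentence is in the past tense, and the general method allows several controls. This part stands only in part. The article names U6 for all five primary endpoints and names nothing else, and the allowance commits the study to no second control.
- **Safeguards exist.** Haemolysed samples are unsuitable, blood is processed within 2 hours, and the models adjust for inflammatory markers. These may reduce a shift, but none measures it.
- **The size can be overstated.** A reader might conclude that normalising to U6 inflates the SD by 1.41, or that a 0.14-cycle shift would make all five miRNAs significant. Neither follows. The 1.41 requires zero correlation between U6 and target CT, whereas removing shared input and extraction variation is what a reference is for, so normalising may equally narrow the intervals. At 0.14 cycle all five are significant together in about 1% to 3% of simulated runs. This part stands in full.

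**Conclusion.** The point holds as an unguarded design risk. The bias is exact algebra from the article's own definitions: any exposure-related difference δ in U6 CT enters all five primary outcomes as a fold change of 2^δ, reaching 1.1 at 0.14 cycle, and the false discovery rate step cannot remove it. Whether such a difference exists is unknown.

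Under the assumed SDs and an 84 vs 84 split, the consequence is modest at 0.14 cycle (at least one false finding in about 10% to 19% of runs, against 4% to 5% with no shift) and severe at 0.5 cycle (76% to 97%). The effect on precision is undetermined, because the correlation between U6 and target CT is not given. The study should act on this because the remedy is cheap and needs to be settled before the association tests, not because the results are known to be compromised.

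**What to change.** Before any association test:

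1. Prespecify at least one further endogenous reference, measured on the stored samples and chosen for stability without sight of the exposure results. Compute the primary ΔCT against the mean of the controls, which section 2.3.3.1 already permits.
2. Report the U6-only and the alternative-reference results side by side as a fixed sensitivity analysis. Averaging alone is not enough: with two controls a U6 shift of δ still leaves δ/2, so 0.5 cycle would still give 2^0.25 = 1.19-fold.
3. Report U6 CT by exposure group and by recorded haemolysis, as an estimate with a confidence interval. Do not use a significance test to decide whether to drop U6. Step 4 of the working shows that such a rule would often miss a small shift, could discard U6 by chance when many exposures are screened, and would make the primary endpoint depend on the data.
4. Interpret same-direction changes across the panel as exposure effects only if they persist under the alternative reference.

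A synthetic spike-in is optional where extraction is still pending. While editing the section, reconcile the sample type, which is plasma in the endpoint definition but serum in the assay description ("serum samples will be thawed, and the circulating RNAs will be extracted"), so that the extra reference is measured in the same material.

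The cost is one more qPCR assay per stored sample and a little more analysis, with no extra patients or visits.

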### Population, inclusion criteria and informed consent

2.2

To address EXPOSITION’s purposes 200 persons with MS attending the Multiple Sclerosis Center of the IRCCS Mondino Foundation, Pavia (Italy) have been selected and recruitment is under way for this study, according to the following inclusion criteria: age ≥18 years; diagnosis of MS according to 2017 McDonald criteria (26); relapsing–remitting (RR) MS, which is the most common MS type and is characterized by alterations of relapses and remission periods (7); routine clinical examinations scheduled in the study period March–April, 2024 and October–April, 2025; Residence in the provinces of Pavia or Milan (Italy); informed consent form signed. Particularly, the study will be conducted in Pavia and Milan, the Northern Italy nodes of the National Biodiversity Future Center (NBFC) (27), which is an Italian research consortium integrating universities, institutes, and stakeholders to study, monitor, and restore biodiversity and to translate evidence into policies, technologies, and nature-based solutions for human and ecosystem health. Thus, Milan represents a large metropolitan and industrial hub with high traffic density, complex socio-economic gradients, and sustained environmental pressures, while Pavia is a medium-sized university city with peri-urban and agricultural interfaces and substantial daily commuting flows to Milan. This paired selection will capture heterogeneous but complementary northern urban exposome profiles within a shared atmospheric basin typical of the Po Valley and characterized by frequent stagnation events.

People refusing to participate in the study will be excluded. Potentially eligible pwMS will be screened by a neurologist, an expert in MS, who will verify that all the inclusion criteria will be fulfilled.

Participants will be selected from the Pavia Database of Multiple Sclerosis of the Multiple Sclerosis Center of the IRCCS Mondino Foundation, Pavia (Italy). It includes 1,400 MS patients, has been active since 1990 and has been part of the ‘Italian Multiple Sclerosis Register’ since 2015.

The study will follow the Declaration of Helsinki. Written informed consent will be obtained from the participants.

Ethical approval was granted by the Ethical Committee of IRCCS Policlinico San Matteo (Pavia) (protocol number: 0040023/23; Accepted: 25/07/2023). The EXPOSITION protocol has been registered on www.clinicaltrials.gov (NCT06325358).

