First, it will be explicitly acknowledged that the current results will not establish national representativeness and will be interpreted as northern benchmarks pending aggregate NBFC analyses (62) in other Italian cities. Indeed, in the EXPOSITION project, (i) the geographical scope will be limited to two cities in Northern Italy, which could limit demographic and environmental representativeness, and (ii) the specific meteorology of the Po-Valley (e.g., atmospheric stagnation, thermal inversions) could amplify exposure contrasts compared to other regions.

Second, a key limitation is the absence of a comparator (non-pwMS) group; by design, the study explores exposome-biomarker heterogeneity within pwMS rather than differences between pwMS and the broader population. Consequently, we cannot determine whether the observed biomarker-exposome relationships are MS-specific or reflect general patterns present in non-MS individuals. This constrains external validity and the specificity of inference. Future work will include non-MS comparators from the general population to directly test disease specificity and enhance the generalizability of the findings.

Last, the scope of variables analysed is constrained, and from a molecular perspective, transcriptomic analysis is restricted to circulating RNA from collected biological samples. Due to the invasive nature of tissue collection, the regulatory role of miRNAs on specific target mRNAs remains speculative, inferred through prior bioinformatic analyses and literature review rather than direct tissue validation. These constraints highlight areas for future research to build upon the study’s findings.

In summary, the EXPOSITION study holds the potential to make a substantial contribution to MS research by elucidating the disease’s environmental determinants and opening avenues for innovative interventions. To strengthen this line of inquiry, future work should directly validate tissue samples to further explore the regulatory role of miRNAs and incorporate a broader set of exposure variables and biomarkers. This comprehensive approach may not only enhance precision medicine for MS but also serve as a model for studying other complex diseases, ultimately advancing both science and public health.

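### The ΔΔCT subtraction is written in the wrong order, so a fold change computed literally from it is the reciprocal of the expression ratio

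*Protocol article*

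**What the plan says.** All three steps of the calculation are in section 2.3.3.1 of the protocol article.

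- On CT: "RT-PCR returns the number of cycles that the samples underwent before they were detected". More miRNA therefore means a lower CT.
- On ΔCT: "ΔCT values are calculated by subtracting the CT value of the endogenous control for a given sample" from the CT of the gene in that sample.
- On ΔΔCT and fold change: ΔΔCT is obtained by taking the ΔCT "of an experimental sample from a control sample. Fold change is calculated by raising 2 to the power of the negative" ΔΔCT.

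The same section names a published comparative-CT method as the one to be used. It ends by announcing an analysis to "highlight the differences in the expression of each miRNA in the two populations", without saying which populations these are.

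Section 2.4.1 makes ΔCT the endpoint measure for each miRNA. It plans to compare mean ΔCT among exposure groups and tests whether the log fold change differs from zero. Section 2.2 enrols "200 persons with MS attending the Multiple Sclerosis Center of the IRCCS Mondino Foundation", and the Discussion says that "a key limitation is the absence of a comparator (non-pwMS) group".

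**The concern.** The ΔCT and ΔΔCT sentences share one construction: subtract the first-named quantity from the second. Applied to ΔCT, this gives the usual gene minus reference. Applied to ΔΔCT, it gives control minus experimental. The minus sign in the exponent then turns the ratio upside down.

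Direction carries meaning in this study. The five miRNAs were selected because their regulation in MS was consistent across databases: three were up-regulated and two down-regulated. Whether an exposure moves a miRNA towards or away from its MS pattern depends on the sign of the change. Section 2.4.5(d) also correlates the validated biomarkers with relative miRNA expression. If that quantity is the fold change as worded, a rank correlation with it has the opposite sign.

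A smaller point of wording is that the text uses a control sample and two populations without saying what they are, in a study where every participant has MS.

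**Working it through.** **Inputs.** From section 2.3.3.1: ΔCT = CT(miRNA) - CT(endogenous control); ΔΔCT = ΔCT(control) - ΔCT(experimental), as worded; fold change = 2^(-ΔΔCT). From section 2.4.1: a fold-change range of 1.1 to 4.5, a minimum of 168 participants and 15% dropout.

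**The plan's own figure.** The disputed text states a formula and no number. The enrolment figure is consistent: 168 / (1 - 0.15) = 197.6, so 198, against the stated 200. The 168 itself cannot be rebuilt from the article, which gives no alpha, dispersion or mean expression. It is not in dispute here.

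**Algebra.** One cycle corresponds to a factor of 2, so expression is proportional to 2^(-ΔCT). The true experimental-to-control ratio is

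R = 2^(-ΔCT(exp)) / 2^(-ΔCT(ctrl)) = 2^(ΔCT(ctrl) - ΔCT(exp)).

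As worded, ΔΔCT = ΔCT(ctrl) - ΔCT(exp) = log2(R), so fold change = 2^(-log2 R) = 1/R.

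With the order reversed, ΔΔCT = ΔCT(exp) - ΔCT(ctrl) = -log2(R), so fold change = 2^(log2 R) = R.

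**Example.** Take ΔCT = 4 in the experimental group and 5 in the control group. The experimental group is detected one cycle earlier and so expresses twice as much. As worded, ΔΔCT = 5 - 4 = 1 and fold change = 2^(-1) = 0.5. Reversed, ΔΔCT = 4 - 5 = -1 and fold change = 2^1 = 2.

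**Over the design range:**

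| True ratio R | ΔΔCT as worded | Fold change as worded | Fold change, order reversed | Natural log fold change, as worded / reversed |
|---|---|---|---|---|
| 1.1 | 0.1375 | 0.909 | 1.1 | -0.0953 / +0.0953 |
| 1.5 | 0.5850 | 0.667 | 1.5 | -0.4055 / +0.4055 |
| 2 | 1.0000 | 0.500 | 2 | -0.6931 / +0.6931 |
| 4.5 | 2.1699 | 0.222 | 4.5 | -1.5041 / +1.5041 |

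**Effect on inference.** The log fold change keeps its size and changes only its sign. A two-sided test against zero gives the same p-value, so power and sample size do not change. As a check, a two-sample calculation on the log2 scale with an assumed SD of 1 and 80% power needs 16 per group for a difference of +1 and 16 for -1. A model fitted directly to ΔCT never uses the ΔΔCT step.

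**The case against.** The strongest defence is that this is a swapped pair of operands in one sentence. The section cites a published comparative-CT method, and a laboratory following that method would not be led astray by the word order. In addition, ΔCT is correctly defined and is the stated endpoint measure, the hypothesis is two-sided, and the primary association is estimated by regression. All of this stands, and it limits the consequence to the direction of fold changes obtained through ΔΔCT. It does not make the sentence right: the article introduces the calculation as the specific procedure and gives the order explicitly.

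A reader might go further and infer that, with no comparator group, there is no control sample and the fold change cannot be computed at all. The documents do not support that. The Discussion rules out only a non-MS comparator. Section 2.4.1 speaks of comparing exposure groups and, for the sample-size dataset, of two groups of people with MS defined by an exposure. Any such group can serve as the reference, and its choice is a detail that an article may leave to the full protocol or analysis plan. Nor do continuous exposures make the section defective, since the regression and penalised models in section 2.4.5 cover them. What remains is loose wording that deserves clarification.

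A reader might also infer that significance tests or the sample size are wrong. They are not, for the reasons shown in the working.

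**Conclusion.** The point holds as an error in a stated formula for the primary endpoints. Followed literally, it returns 1/R in place of R: 0.5 for a doubling, and 0.909 to 0.222 across the design range of 1.1 to 4.5. Up-regulation would be reported as down-regulation and the reverse, for each of the five miRNAs.

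This rests on two things: the ordinary meaning of subtracting one quantity from another, which the ΔCT sentence uses correctly, and the analysis following the written order. The article does not show which order the laboratory or the code uses, so it cannot be said that results will in fact be inverted. The undefined control sample and two populations call for clarification only and are not a contradiction of the design.

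**What to change.** 1. In section 2.3.3.1, write ΔΔCT = ΔCT(index exposure group) - ΔCT(reference exposure group within the MS sample), with fold change = 2^(-ΔΔCT).
2. Check that the analysis code uses this order. A one-line test is enough: index ΔCT 4 and reference ΔCT 5 must return 2, not 0.5.
3. Where a linear, identity-link model is fitted to ΔCT, state that a positive coefficient β means lower expression, and report 2^(-β) as the fold change. Do not apply this to the negative binomial models that the article also names: under their usual log link, β is a log ratio of mean ΔCT, and 2^(-β) is not a fold change in expression.
4. As a clarification, replace the control sample and the two populations with the reference and contrast exposure groups within the MS sample.

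The cost is a few sentences of wording and a short code check. Design, sample size and testing stay as they are.
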